### 5.5.1 Handling of Discontinuation of SP and Early Terminations

If the PI discontinues a patient from SP due to development of an AE, the patient wishes to withdraw from the study, or the patient is terminated from the study for any other reason every effort should be made to:

- Complete the Early Termination visit assessments, as directed in the SOA ([Table 1](#))
- Monitor the patient for resolution of any existing AEs, and onset of new AEs for 3 weeks (21 days) after the last dose of SP.

The data should be documented on the appropriate eCRF in the electronic database capture (EDC) system.

If, due to extenuating circumstances, the PI and/or study site team are concerned that the patient may not be able to safely complete all the required visits and assessments the PI should contact the Sponsor's Medical Monitor to discuss whether an early termination visit should occur to enable the return of the SP, and the completion of key end of intake assessments/measures, while ensuring the patient's safety.

### 5.5.2 Premature Termination or Suspension of Study

This study may be suspended or prematurely terminated at the Sponsor's discretion. Written notification documenting the reason for study suspension or termination will be provided by the Sponsor to the PI. If the study is prematurely terminated or suspended, the PI will promptly inform the Institutional Review Board (IRB) and will provide the reason(s) for the termination or suspension.

Circumstances that may warrant termination or suspension include, but are not limited to:

- Determination of unexpected, significant, or unacceptable risk to patients as determined by the ongoing review of aggregate safety data by the medical monitor

Circumstances that may warrant termination or suspension of an individual site include but are not limited to:

- Insufficient compliance with protocol requirements by the site
- Site submits data that are consistently insufficient, incomplete, and/or unevaluable

If the study is suspended temporarily at a site, the study may resume once concerns about safety, protocol compliance, and/or data quality are addressed and satisfy the Sponsor and/or IRB.

### **5.5.3 Lost to Follow-up**

A patient will be considered lost to follow-up if he or she repeatedly cannot be contacted for scheduled telemedicine visits or sample collections and is unable to be contacted by the study site.

If a patient fails to attend a required study visit, the site must:

- Attempt to contact the patient and reschedule the missed visit as soon as possible
- Counsel the patient on the importance of maintaining the assigned visit schedule
- Ascertain whether the patient wishes to and/or should continue in the study

Before a patient is deemed lost to follow-up, the PI or designee must make every effort to regain contact with the patient until the end of the study, including potentially contacting the emergency contact listed by the patient. These contact attempts should be documented in the patient's study record. Should the patient continue to be unreachable, he/she will be considered lost to follow-up.

## **6 STUDY PRODUCTS**

### **6.1 Description of Study Product**

#### **6.1.1 KB109**

As depicted in [Figure 5](#), KB109 is a mixture of polymers of glucose, galactose, and mannose in proportions of approximately 45%, 45%, and 10%, by weight respectively. The formula is  $H-[C_6H_{10}O_5]_n-OH$ , where the total number of monomer units in a single polymer of the mixture ranges from 2 to approximately 60 ( $n = 2-60$ ), with a mean value for the mixture of approximately 12.6 monomer units. Each monomer unit may be unsubstituted, singly, doubly, or triply substituted with another glucose, galactose, or mannose unit by any glycosidic isomer.

**Figure 5 KB109 Structure**

[figure not shown]

## 6.2 SP Dosing, Preparation and Administration

Patients randomized to SSC + KB109 will consume their SP orally BID (at least 8 hours apart). Preparation of the SP involves adding 120 mL of water into a glass/container, instilling the directed amount of SP powder on top, and mixing to dissolve prior to drinking as a beverage. The SP should be consumed within 1 hour after reconstitution.

Dosing of KB109 is detailed in [Table 3](#).

**Table 3. Dose Up-titration of the Study Product**

| SP Administration Period | Dose (KB109)        |
|--------------------------|---------------------|
| Days 1–2                 | 9 g BID (18 g/day)  |
| Days 3–4                 | 18 g BID (36 g/day) |
| Days 5–14                | 36 g BID (72 g/day) |

Abbreviations: BID: Twice daily; SP: Study Product.

Doses should be taken at the same time each day. The morning dose should be taken by noon each day, and the evening dose should be taken approximately 8 hours after the morning dose. A missed morning dose may still be taken before noon on the same day; a missed evening dose may be taken within 4 hours of the routine daily evening administration dose.

Details of the patient's SP dosing (including the date, approximate time, and amount) will be recorded in SP dosing logs.

### **6.3 SP Storage and Accountability**

The SP is to be dispensed by the trained team at the storage and shipping vendor. Patients will be instructed to return used and unused SP to the storage and shipping vendor, per the instructions included in the SP packaging. At the termination of the study or at the request of the Sponsor, the storage and shipping vendor will destroy or return unused SP and all partially dispensed or empty packets.

### **6.4 Unblinding**

This is an open label study. There are no requirements for unblinding.

### **6.5 Concomitant Medications/Dietary Supplements**

All concomitant medications and dietary supplements taken after consent is provided will be recorded. Medications to be reported include all prescription medications, over-the-counter medications, and other non-prescription medications taken by a patient during study participation. All dietary supplements taken by patients during study participation will be reported as well. For this study, a prescription medication is defined as a medication that can be prescribed only by a properly authorized/licensed clinician.

Information regarding eligibility criteria relating to the use of certain medications can be found in [Section 5.1](#) and [Section 5.2](#) of the protocol.

See [Section 6.6](#) for prohibited medications and dietary supplements.

### **6.6 Prohibited Medications/Dietary Supplements**

Medications or dietary supplements prohibited at screening and during the study provided that appropriate safety considerations are followed, including:

- GI increasing motility agents such as stool softeners, laxatives, or fiber supplements within 7 days prior to screening and during the study (intake period and follow up).
- Antacid (H2 blockers and PPIs) and antidiarrheal agents are not prohibited
- Systemically administered immunosuppressant medications 3 months of study screening and during the study (intake period and follow up)
- Therapy with any immunomodulatory agent 12 months previous of study screening and during the study (intake period and follow up)

- Systemic antibiotics, antifungals, or antivirals for treatment of active infection 14 days previous of study screening and during the study (intake period and follow up)

Note: Prebiotics and/or probiotics intake is permitted provided the patient has been taking them consistently in the 28 days prior to screening and continues to do so during the study (i.e., no changes in dose, frequency, or type of prebiotic/probiotic). Patients not taking prebiotics and/or probiotics at study entry are prohibited from initiating them during the study. There are no restrictions on diet.

Additionally, other medications NOT listed that would interfere with the objectives of this study, pose a safety risk, or confound the interpretation of the study results (in the PI's judgement) are prohibited while a patient is participating in the study.

Should circumstances that require use of prohibited medications arise (such as anti-viral or immunomodulating medications), the PI (in consultation with the Medical Monitor and the Sponsor) will make the assessment whether to discontinue the patient from the study for the patient to receive any necessary and appropriate medical care.

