### 3.2.2 Secondary Endpoints

The secondary endpoints are as follows:

- Time to resolution of overall 13 COVID-19 related symptoms which is defined as from Day 1 until the day at which the overall composite score of 13 COVID-19 related symptoms becomes 0 or 1 and remains at 0 or 1 for the rest of the Intake Period and for the Follow-up Period. Overall composite score of 13 COVID-19 related symptoms is the sum of 13 COVID-19 related symptom scores (i.e., cough, chills/repeated shaking with chills, muscle pain, fever, headache, anosmia/ageusia, shortness of breath, sore throat, gastrointestinal disturbance/symptoms, diarrhea, fatigue, nasal congestion, and chest tightness (CDC 2020). Each COVID-19 symptom will be recorded by patients on a scale of 0: Absent, 1: Mild, 2: Moderately severe, 3: Very severe. The overall composite score ranges from 0 (no symptoms) to 39 (very severe)
- Time to resolution of overall 8 cardinal COVID-19 related symptoms which is defined as from Day 1 until the day at which the overall composite score of 8 cardinal COVID-19 related symptoms becomes 0 or 1 and remains at 0 or 1 for the rest of the Intake Period and for the Follow-up Period. Overall composite score of 8 cardinal COVID-19 related symptoms is the sum of 8 cardinal COVID-19 related symptom scores (i.e., cough, chills/repeated shaking with chills, muscle pain, fever, headache, anosmia/ageusia, shortness of breath, and sore throat)
- Proportion of patients with reduction from Baseline (symptom present at Baseline) in each of 13 individual COVID-19 related symptom at EOI and Follow-up
- Proportion of patients with symptom becomes absent (symptom present at Baseline) at EOI and Follow-up for each of 13 individual COVID-19 related symptom
- Change from Baseline to EOI in overall composite score of 13 COVID-19 related symptoms
- Change from Baseline to EOI in overall composite score of 8 cardinal COVID-19 related symptoms
- Time to resolution of fever (defined as from Day 1 until the day at which a patient's daily maximum temperature achieves and remains below 100.4 °F for the rest of the Intake Period and for the Follow-up Period without an antipyretic medication)
- Proportion of patients with oxygen saturation <95% on Day 14 and Day 35

- Proportion of patients with oxygen saturation <98% on Day 14 and Day 35
- Measures collected from the Healthcare Provider Wellness Visits

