## Part 2, Follow-up Period

On Day 15, all patients will enter the Follow-up Period (Days 15 to 35) where COVID-19 signs, symptoms and healthcare utilization indices will be collected weekly in TrialPace™ where appropriate. On Day 14, the Investigator will instruct the patients to stop the intake and return the SP during the Follow-up Period (Days 15 to 35). In addition, wellness visits by telephone call will be conducted on Days 21, 28, and 35 to follow-up on the patient's health status.

On Day 35, all patients will undergo another telemedicine visit where the following will be conducted: an abbreviated physical examination, an assessment of safety and other protocol-specified measures of health, and an evaluation of whether follow-up treatment is recommended. When wellness and telemedicine visits fall on the same day, they will be combined as a telemedicine visit. If feasible blood samples for clinical chemistries, biomarkers and serological measures of immunity, and nasal/oropharyngeal swabs for quantitative viral load assessments (research purposes only) will be collected; sample collection may occur at the patient's home by a healthcare professional, remotely, or at the study site or clinic.

For convenience, standard terms language included in International Conference for Harmonization (ICH) guidance relevant to the conduct of clinical trials are used in this protocol. An example of such a term used in this protocol is "treatment emergent," included in ICH E9. Use of this standard term is not intended to connote treatment with a medicinal product administered (ICH E9 2018).

Throughout the study, safety will be monitored by TEAEs, clinical signs and symptoms, and selected vital signs (i.e., temperature and oxygen saturation). Concomitant medications/supplements will be recorded throughout the study. Any patient experiencing a TEAE, or intolerable GI symptoms will be evaluated by the principal investigator (PI) or telemedicine provider for possible interruption and/or down-titration of SP dose to the previously tolerated level in consultation with the medical monitor.

In the event of significant worsening of COVID-related symptoms or two sequential pulse oximetry readings of <94% within 2 minutes, patients will be instructed to seek medical attention immediately (see [Section 6.7](#)).

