#### **4.3.7 Healthcare Utilization**

From Day 2 onwards, patient-assessed measures of healthcare utilization will be performed every morning upon waking until the end of the study (Intake Period plus Follow-up Period) (Table 1).

Measures will include:

- Prescription Medication Use – recorded as reason, type, dose and frequency
- Over-the-counter Medication Use – recorded as reason, type, dose and frequency
- Supplement Use – recorded as reason, type, dose and frequency
- Emergency room or Urgent Care visit – Rated as Y/N; if Y then reason will be recorded
- Medical provider visit – Rated as Y/N; if Y then reason as well as if this is a visit for a co-existing condition (mental health visit, physical therapy, etc.) will be recorded;
- Hospital stay – Rated as Y/N; if Y then reason will be recorded

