### **5.5 Withdrawal of Patients**

Patients have the right to withdraw from the study at any time for any reason, without giving a reason and without penalty or loss of benefits they are entitled to. The investigator also has the right to withdraw patients from the study if this is in the best interest of the patient.

Patients will be discontinued from the study in the event of any of the following:

- Patient independently withdraws consent from the study (e.g., patient declines further participation in the study)
- PI determines that the patient has developed a concurrent illness, condition, or an AE due to which continued participation in the study and/or SP dosing is considered potentially harmful to the patient and withdrawal is in the best interest of the patient
- Patient discontinues from SP dosing (i.e., due to development of an AE), but continues his/her consent to participate in the study for follow-up only (e.g., for continued collection of AE information)
- Patient failure to comply with study requirements (e.g., failure to properly consume the SP or failure to comply with other protocol-specific assessments) resulting in protocol deviations that make the interpretation of the data not feasible
- Patient becomes pregnant

Patient requires hospitalization due to worsening COVID-19

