## 6.7 Self-supportive Care

Patients with COVID-19 should follow the steps as instructed by their healthcare provider (consistent with guidance from the CDC, local ordinances or practices) to care for themselves and to help protect other people in the home and community from potentially getting sick ([CDC 2020](#)).

In order to manage the symptoms associated with COVID-19, over-the-counter cough, cold, and anti-pyretic medications can be used as necessary by patients in accordance with their respective drug facts label or as instructed by their healthcare provider.

The brand name, generic name, dose, and time must be recorded for every usage occasion.

Since this is an out-patient based study, in the event of significant worsening of COVID-19-related symptoms or two sequential pulse oximetry readings of <94%, patients will be instructed to seek medical attention immediately with their treating provider or go to the emergency room. If the PI or study staff are contacted due to significant clinical worsening of COVID-19 symptoms, the patient will be triaged appropriately to the emergency room or to the outpatient treating provider per clinical judgement. The patient will be removed from the study only if hospitalized (refer to [Section 5.5](#)).

Patients will be provided with information consistent with CDC guidance regarding emergency warning signs for COVID-19 ([CDC 2020](#)) instructing them to seek medical attention immediately, if any of the following occur:

- Trouble breathing
- Persistent pain or pressure in the chest
- New confusion or inability to arouse
- Bluish lips or face

A medical provider must be contacted for any other symptoms that are severe or concerning to the patient. Patients will be instructed to call 911 if they have a medical emergency and be instructed to notify the operator that they have, or think they might have, COVID-19.

Patients will be instructed to put on a cloth face covering before medical help arrives.

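### No section clearly lets a patient stop KB109 for good and stay in full follow-up; when a prohibited drug is needed, Section 6.6 names only leaving the study

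*Protocol*

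**What the plan says.** Section 6.6 prohibits systemic antibiotics, antifungals and antivirals for active infection, immunomodulators, immunosuppressants and motility agents through intake and follow-up. It adds any other drug that the PI judges would confound the results. The ban applies to both arms. If such a drug becomes necessary, the PI, in consultation with the Medical Monitor and Sponsor, "will make the assessment whether to discontinue the patient from the study for the patient to receive any necessary and appropriate medical care". No other action is named.

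Related text elsewhere in the protocol:

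- Section 5.5 lists events for which a patient is discontinued from the study. One is the patient who stops KB109 but "continues his/her consent to participate in the study for follow-up only"; collection of AE information is the example given.
- Section 5.5.1 begins "If the PI discontinues a patient from SP due to development of an AE" and treats that patient together with those who leave the study. It asks for the early termination (ET) assessments and for monitoring of existing AEs and "onset of new AEs for 3 weeks (21 days) after the last dose of SP".
- Section 6.7, on worsening COVID-19, says "The patient will be removed from the study only if hospitalized".
- Section 6.8 allows KB109 to be reduced or temporarily interrupted for worsening COVID-19 or attributable AEs. A patient who cannot tolerate the lowest dose may be withdrawn from the study.
- Section 3.2.2 counts symptoms as resolved only if the composite score "remains at 0 or 1 for the rest of the Intake Period and for the Follow-up Period".

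**The concern.** Stopping the product and leaving the study are different decisions, and the protocol does not keep them apart. A patient who needs an antiviral, an immunomodulator or an antibiotic may be doing worse than average. If that patient is removed, later data are missing for a reason that may be linked to outcome, and the decision is taken with the arm known. In the SSC-alone arm there is no product to stop, so the only choice that 6.6 offers is to leave or to stay.

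The endpoints at stake are secondary and exploratory: sustained symptom and fever resolution, change to end of intake (EOI), Day 14 and Day 35 oxygen saturation, quality of life (QOL) and healthcare utilization. An analysis plan can choose how to handle missing values, but it cannot recover values that were never collected. The collection rule therefore belongs in the protocol.

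**Working it through.** **The plan's own figure.** Section 8.1 allows 15% attrition from all causes. 350 × 0.85 = 297.5, or 148.75 per group (stated: 296 and 148, which is 148.75 rounded down). 400 × 0.85 = 340, or 170 per group (stated: the same). The allowance is therefore 0.15 × 175 = 26.25 to 0.15 × 200 = 30 patients per arm. Each removed patient is 1/200 = 0.50% to 1/175 = 0.57% of an arm. The protocol does not say how much of the allowance is for prohibited drugs.

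**What remains after removal.** The ET column of Table 1 includes symptoms, temperature, oxygen saturation, PGIC, utilization and bedrest, but not QOL, blood samples or swabs. After that visit, only AEs are followed.

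**Inputs for the loss per patient.**

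- Intake diary: Days 1–14, 14 entries.
- EOI: the average over Days 12–14 (Section 8.4.3).
- Composite-score model windows: Days 2–4, 5–11 and 12–14 (Section 8.4.3).
- QOL: Days 14 and 35 (Section 4.3.6).
- Utilization: two readings, because the sections differ. Section 4.1 says that in follow-up "COVID-19 signs, symptoms and healthcare utilization indices will be collected weekly", giving Days 2–14 (13) plus Days 21, 28 and 35 (3) = 16 entries. Section 4.3.7 says "every morning upon waking until the end of the study", giving Days 2–35 = 34 entries.

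**Formulas**, for exit with an ET visit on Day d (d is an assumption):

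- Intake diary lost: (14 − d)/14 for d up to 14, otherwise 0.
- Utilization lost, weekly reading: (14 − d + 3)/16 for d up to 14; 3/16 for d from 15 to 20.
- Utilization lost, daily reading: (35 − d)/34.

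| Exit day | Intake diary lost | Model windows kept | EOI days lost | Utilization lost, weekly | Utilization lost, daily | Oxygen saturation and QOL lost |
|---|---|---|---|---|---|---|
| 3 | 11/14 = 79% | 1 of 3 | 3 of 3 | 14/16 = 88% | 32/34 = 94% | Days 14 and 35 |
| 6 | 8/14 = 57% | 2 of 3 | 3 of 3 | 11/16 = 69% | 29/34 = 85% | Days 14 and 35 |
| 10 | 4/14 = 29% | 2 of 3 | 3 of 3 | 7/16 = 44% | 25/34 = 74% | Days 14 and 35 |
| 20 | 0/14 = 0% | 3 of 3 | 0 of 3 | 3/16 = 19% | 15/34 = 44% | Day 35 only |

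The EOI window is lost completely only when exit comes before Day 12. Sustained resolution through follow-up cannot be confirmed in any of the four rows, because even a Day 20 exit misses the Day 21, 28 and 35 entries.

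**Possible bias, illustration only.** Suppose a fraction q of an arm is removed before resolving and treated as non-informatively censored, 80% of the others resolve by Day 35, and a fraction r of those removed would have resolved. The arm's resolution rate is then overstated by about q × (0.80 − r). For q = 2% and r = 60% this is 0.02 × 0.20 = 0.4 percentage points. For q = 15% and r = 40% it is 0.15 × 0.40 = 6 points. For r = 80% it is zero. None of these values comes from the protocol, and q = 15% gives the whole attrition allowance to this one cause.

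**Primary endpoint.** AE monitoring runs for 21 days after the last dose. A completer's window has the same length (Day 14 to Day 35). A patient whose last dose was on Day 6 would be followed to Day 27. Section 7.1 also requires AEs to be followed to closure whether or not the patient is still participating. One gap remains: an SSC-alone patient has no last dose from which to count the 21 days.

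**The case against.** The strongest reply is that retention is already permitted. Section 6.6 asks whether to discontinue, so keeping the patient is one of two outcomes. Section 6.8 lets KB109 be interrupted, with the patient still in the study, for worsening COVID-19. Section 6.7 then limits removal of such patients to hospitalization. For drugs unrelated to COVID-19, such as a laxative or an antibiotic for another infection, the case for informative loss is weak. Any bias within an arm carries over to the comparison only if removal, or the prognosis of those removed, differs between arms. The study is descriptive and open label, and its primary endpoint concerns safety.

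Most of this stands, and it rules out several stronger readings that a reader might infer:

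- *That a prohibited drug forces withdrawal.* It does not; 6.6 leaves it to judgment.
- *That 6.6 and 6.7 contradict each other throughout.* They conflict in one case only: an outpatient with worsening COVID-19 who is prescribed a prohibited drug.
- *That every removal loses the EOI data.* The ban runs to Day 35, and a removal after Day 14 loses none of them.
- *That the primary endpoint is compromised.* The AE provisions largely protect it.

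The reply does not remove the gap. The interruption in 6.8 is temporary and is not triggered by a prohibited drug as such. The follow-up-only wording in 5.5 might look like the missing route, but it sits in the list of reasons for study discontinuation. Followed as written, it takes out of the study patients who agreed to stay.

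**Conclusion.** The point holds as a weakness of design and wording that should be corrected, with medium confidence. The protocol permits but does not require removal for a prohibited drug. It has no clear provision for permanent discontinuation of KB109 with full follow-up, and it classes the nearest such case as study discontinuation. Where these rules are used, secondary and exploratory data after the ET visit are lost, possibly in relation to outcome.

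The size per removed patient is as tabulated and depends on the assumed exit day and, for utilization, on which collection frequency applies. The total effect cannot be computed, because the protocol gives no rate of prohibited-drug use or of removal. The 0.4 to 6 point illustration shows only what would follow from the assumed values and is not an estimate for this trial.

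**What to change.** **Section 6.6.** State that need for a prohibited drug is recorded as a concomitant medication and is not by itself a reason to leave the study in either arm. The PI, with the Medical Monitor, decides separately whether KB109 continues. Diary, wellness calls, Day 14 and Day 35 visits, AEs and healthcare utilization continue to Day 35 unless consent is withdrawn. Leave any protocol deviation to the existing process in Section 9.3. Labelling necessary treatment a deviation in advance is not needed and sits awkwardly with that section's statement that none are preapproved.

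**Section 5.5.** Move stopping KB109 with continued consent out of the study-discontinuation list, so that these patients stay in full follow-up.

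**Section 5.5.1.** Apply the ET visit only to patients who leave the study.

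Keep Section 6.7 and the right to withdraw a patient in the patient's best interest. Removal on hospitalization for COVID-19 is a separate rule that this change does not touch.

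**Cost.** Amended wording in three sections, with IRB approval. The remote procedures and the concomitant-medication record already exist. The downside is that some retained data are collected under added treatment, which is already recorded.
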